### Intervention

#### Standard care

In all wards during baseline assessment and in control wards during the intervention phase, patients will receive standard pharmaceutical care from a pharmacy team in the traditional role of taking the responsibility for the appropriate, safe and cost-effective use of medication from a central pharmacy. This does not include patient contact or direct access to patients' medical records, nor does it include face-to-face contact with the ward doctors or nurses. The activities regarding individual patient pharmaceutical care consists of provision of community pharmacy data to the ward at admission, daily screening of alerts generated by the CPOE-system by the pharmacists during hospitalisation and provision of a discharge medication list for the community pharmacy.

#### Ward-based pharmacy care

A clinical pharmacy team will perform the ward-based pharmacy interventions. This team consists of pharmacy practitioners (pharmacy technicians, who completed additional training for ward-based pharmacy interventions) and hospital pharmacists.

Patients admitted at an intervention ward will receive bedside care from the ward-based pharmacy team. These interventions are tailored to cover critical steps in the medication process during the surgical pathway. On admission the pharmacy practitioner will perform medication reconciliation in consultation with the patient. This includes verification of the current use of community pharmacy medication. During hospitalisation the hospital pharmacist will review the medication charts daily and will optimise drug therapy when needed. The pharmacist combines information from CPOE-alerts, laboratory results and medical record information, in liaison with the ward doctor (face-to-face communication). At discharge the pharmacy practitioner will review the medication prescriptions by comparing them with the medication at admission. Unintended discrepancies will be discussed with the ward doctor. In addition, the pharmacy practitioner will perform patient counselling and send a complete list of discharge medication to the community pharmacy and general practitioner.

### Study outcomes and data collection

The primary outcome parameter is the number of preventable ADEs per 100 admissions. Secondary outcome parameters are severity of preventable ADEs, number of patients with preventable ADEs per total number of admissions, direct (non-)medical costs and indirect non-medical costs, extra costs per prevented ADE, number and type of pharmacy interventions, length of hospital stay, complications registered in a national complication registration system for surgery, number of readmissions within three months after the initial admission (follow-up), quality of life during follow-up and number of non-institutionalized days during follow-up.

To assess the incidence and severity of preventable ADEs, we will systematically evaluate patient records and the hospital information system by use of a developed and validated Trigger Tool. This tool is based on previously literature on trigger tools, such as the trigger tool for measuring harm in ICU patients [22], the trigger tool for detection of AEs in surgical patients [23] and the widely used Global Trigger Tool of the Institute for Healthcare Improvement [24,25]. This list of items, or triggers, are clues to identify potential pADEs. Previous studies have shown that a trigger tool can efficiently and consistently be applied to detect and identify preventable ADEs [26,27]. If patient records are positive for potential pADE triggers, an independent expert panel, consisting of senior hospital pharmacists and consultant surgeons, will assess the presence or absence of the potential pADE individually, blinded for the hospital and ward the patient was admitted to. They will determine the presence or absence by use of a causality assessment tool for surgical patients based on tools such as the Naranjo probability score and the WHO-UMC [28,29].

Besides causality assessment, the expert panel will also determine the severity of the ADE by use of a classification system called Common Terminology Criteria for Adverse Events (CTCAE) developed by the U.S. National Cancer institute [30]. This list is preferred, because a grading scale is provided for each AE term, in contrast to the National Coordinating Council for Medication Error Reporting and Prevention index (NCC MERP) [31]. Furthermore, the expert panel will assess the additional impact of each pADE to a patient's life, given his disease status. Discrepancies between the individual assessments will be discussed at consensus meetings of the experts.

For the economic evaluation, we will collect direct medical costs of all included admissions, such as diagnostic examinations, therapeutic interventions as well as the costs of monitoring by hospital pharmacists during hospitalization. Most data will be extracted from the hospital information system. Specifically, registration of tasks performed by the clinical pharmacy team will be done, not just as input values for the cost estimates, but also to support implementation decisions in anticipation of the program's cost-effectiveness. Moreover, we will gather information on direct (non-)medical costs, such as costs of out-patients care, out-of-hospital care and, if opportune, readmissions, as well as on indirect non-medical costs, such as productivity losses, by sending a patient questionnaire at three months following hospital admission. This questionnaire consists of an adapted version of the Health and Labour questionnaire developed by the Institute for Medical Technology Assessment in the Netherlands [32].

Besides cost-related questions, the validated EQ-5D questionnaire is used at three months after the initial admission to measure the quality of life of the patient [33]. The EQ-5D instrument contains five dimensions (mobility, self care, usual activities, pain/discomfort and anxiety/depression) for which patients have to indicate whether they experienced no, some or severe/extreme problems. In addition, patients have to assess their health status on a Visual Analogue Scale (VAS), ranging from zero for the worst imaginable health state to 100 for the best imaginable health state [33].

During the intervention period, we will document all interventions in the intervention wards performed by the clinical pharmacy team. In this study an intervention is defined as every change made in the patient's farmacotherapeutic management due to advice of one of the pharmacy team members. These interventions will be documented using a classification that is based on previous described types of interventions in literature [34]. The categories of this classification are listed in table 1.

**Table 1 T1:** Types of interventions

Intervention	Including
Provision of drug information	physicians and nurses

Change route of administration	e.g., intravenous to oral

Drug dosage adjustment	sub- or supratherapeutic

Drug frequency adjustment	sub- or supratherapeutic

Recommendendation of monitoring	drug interaction, toxicology, allergy, adverse drug events

Suggest initiation of drug therapy	untreated indication

Recommendation of alternative drug therapy	formulary changes, drug interaction

Suggest discontinuing drug therapy	toxicology, allergy, adverse drug event, drug duplication

Others	not listed above

### Sample size and data analysis

The power calculation is based on the parallel comparison of the number of pADEs per 100 admissions between patients admitted at the intervention ward (with ward-based pharmacy care) and those admitted at the control ward (with standard care). We expect a mean base rate of five preventable ADEs per 100 admissions in the control group. This rate is conservatively estimated, based on the incidence of pADEs per 100 admissions in prospective observational studies in hospitalised patients (pooled mean 2.1%, range: 0.6%-16.2% [4,6-14]) and observed rates in control groups of intervention studies on the effect of clinical pharmacy on pADEs (pooled mean 11.6%, range: 11.4%-12% [16,17,26,35]). The difference in incidence rate between the observational and intervention studies can be predominantly explained by a higher sensitivity of ADE detection methods employed in the intervention studies.

In this study population, we hypothesize a relative reduction in pADEs of 60%. This hypothesis is based on the findings of two controlled studies assessing ward-based pharmacy in non-surgical wards, showing a reduction of 66% and a reduction of 78% [16,17].

With all admissions equally distributed over intervention and control wards, a sample of 964 admissions achieves 80% power at a 0.05 one-sided significance level to detect a reduction in the number of pADEs per 100 admissions from 5 to 2 or below (rate ratio <0.4), resulting from ward-based pharmacy care compared to standard care. To control for ward-specific ADEs at baseline, 480 patients equally distributed over the participating surgical wards, will be included at start. Hence, the total number of patients amounts to 1444 (480 + 964). This number of patients will be distributed over the participating centres according to their proportion of number of admitted patients in the wards.

With the total number of 1444 patients a Poisson regression of the number of pADEs with the type of treatment (intervention or control) as the main covariate of interest can be performed to detect a rate ratio below 0.4 with 80% power at a significance level of 0.05. This is performed while adjusting for other covariates like, for instance, hospital site, ward type, observation period, ADE levels at baseline, and patient age, even if these other covariates explain as much as 50% of the variance in pADE counts by type of treatment.

Because the number of pADEs per 100 admissions in the control condition is probably conservatively estimated, a recalculation of the needed sample size will be performed when the baseline pADE counts become available.

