## Methods/Design

### Design

To answer the research questions, a multi-centre controlled trial, with randomisation at ward-level is designed. Participating centres are the Academic Medical Centre (AMC), the Onze Lieve Vrouwe Gasthuis (OLVG) in Amsterdam and the Diakonessenhuis in Utrecht. In each centre at least two surgical wards will participate. These study wards contain mainly gastro-intestinal and vascular surgical patients.

The study design is depicted schematically in figure 1. First, baseline assessments in each hospital in the participating surgical wards will be performed. Then, in each centre, one ward will be randomly assigned (one-time randomisation) as intervention ward, receiving ward-based pharmacy care, whereas the other ward(s) will serve as control ward, receiving standard pharmaceutical care from the central hospital pharmacy (i.e. current daily practice).

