## Discussion

Measuring cost-effectiveness of clinical pharmacy is complex. Criteria for such research are not standardized. Recently, several recommendations have been stated in a systematic review [21], such as comparative design including a control group, providing details of clinical pharmacy interventions, considering health benefits, considering the effect of program factors (e.g. type of ward and hospital, and level of expertise of clinical pharmacist), considering applicability in other settings, taking a societal perspective when evaluating clinical pharmacy interventions, and including sensitivity and incremental cost-effectiveness analyses. The present study design meets these criteria.

For this study we choose a parallel design with preceding baseline assessment and with randomisation at ward level to assess the incidence of pADEs at baseline in the participating study wards and to determine the impact of the ward-based pharmacy care as well as to take into account the impact of differences between the observed study wards. Furthermore, a large number of factors are suggested to increase the risk of ADEs in hospitalised patients, such as drug characteristics (e.g. route of administration), patient-specific factors (e.g. number of medications taken) [9] and organisational factors (e.g. communication) [38]. These drug characteristics, patient-specific and organisational factors influence the incidence and severity of ADEs, but it is unknown to what extent. Therefore, the ideal situation to test the impact of a pharmacy team on clinical and economic outcomes would consist of an equal distribution of all these factors in experimental and control group. Straightforward comparison of two wards, with one ward only experimental and the other ward only control patients, implies the risk of unbalanced confounders because of the differences between the wards, patients and its staffing. By adding a baseline assessment it is possible to adjust for a priori differences between wards. In this manner a clear insight of the sole impact of the ward-based pharmacy care on pADEs is obtained.

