We choose not to randomise at patient level within a ward because this would imply that one medical team provides care to both experimental and control patients concurrently. The drawback of this design is that the medical staff confronted with the pharmacy team has an increased awareness level of medication safety while they are treating control patients at the same time. This effect is know as the 'Hawthorne effect'--affecting the standard care in control patients [39]. In other words, experimental and control patients in one ward together implies a substantial risk of contamination of arms and thus blurring of effects on outcomes. Therefore, we choose a randomised design on ward level. Thus, in each participating centre, one ward is assigned as experimental (intervention) ward, whereas the other(s) will serve as control ward.

To reduce the risk of confounding, a spaced randomised design including 'cross over' would be desirable. Hereby each ward will serve as control and experimental ward separated with a wash-out period. However, this design was considered of limited value, because wash-out of learning experiences in the intervention arm at a ward during latter sequence might not be successful and the control period might thus become biased. Furthermore, this design is time consuming and may not be needed if extensive baseline assessments are done. Moreover, because of the long wash-out period needed, uncontrolled and unknown changes in factors associated with the risk of ADEs may have occurred.

The participation of three different types of hospitals, an university teaching hospital, a large teaching hospital and a community hospital, strenghtens the general applicability and effectiveness of ward-based pharmacy to various clinical settings.

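### Wards are randomised, but the stated Poisson regression and both sample sizes treat admissions as independent, so the primary p-value, confidence interval and 80% power are too optimistic

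*Protocol article*

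**What the plan says.** All references are to the protocol article.

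- **Allocation (Design).** After a baseline assessment, "in each centre, one ward will be randomly assigned (one-time randomisation) as intervention ward"; the remaining ward or wards in that centre are controls. On numbers: "In each centre at least two surgical wards will participate". Three centres take part, so there are three intervention wards and at least six wards in all.
- **Sample size (Sample size and data analysis).** "We expect a mean base rate of five preventable ADEs per 100 admissions in the control group". The 964 admissions, split equally between arms, are said to give 80% power at one-sided 0.05 "to detect a reduction in the number of pADEs per 100 admissions from 5 to 2 or below (rate ratio <0.4"). A further 480 baseline patients, spread equally over the wards, bring the total to 1444.
- **Model (same section).** "With the total number of 1444 patients a Poisson regression of the number of pADEs with the type of treatment (intervention or control". Treatment arm is the term of primary interest. Hospital site, ward type, observation period, baseline ADE level and age are given as examples of adjustment, and the covariates may explain up to 50% of the variance.
- **Clustering.** The article mentions no intracluster correlation, design effect, ward random effect, robust variance or ward-level test. The planned sample size recalculation is motivated by the base rate alone.
- **Discussion.** Comparing wards directly "implies the risk of unbalanced confounders because of the differences between the wards, patients and its staffing". The baseline assessment is offered as the remedy.

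**The concern.** When wards are randomised, the error relevant to the treatment comparison includes how much wards differ from each other and how differently they change over time. A Poisson regression on admissions estimates its standard error from event counts alone. Any ward variation left after adjustment is then credited to the pharmacy team with too much certainty.

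This affects the p-value and confidence interval of the primary outcome. It also affects the stated uncertainty of the pADE difference, which is the denominator of the incremental cost-effectiveness ratio. It is not a detail left to an analysis plan, because the article itself fixes the model, the numbers, the significance level and the power.

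**Working it through.** **1. Reproducing 964.** Inputs from the article: rates 0.05 and 0.02, one-sided 0.05, power 80%, equal arms. For two independent Poisson rates,

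n per arm = (1.645 + 0.842)² × (0.05 + 0.02) / (0.05 − 0.02)² = 480.9, total 962.

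This is within 2 of 964 and contains no allowance for wards.

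**2. Reproducing 1444.** Using the Signorini formula for Poisson regression with a binary covariate, 1:1 allocation, base rate 0.05, rate ratio 0.4 and R² = 0.5:

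N = (1.645 × √4 + 0.842 × √7)² / (0.05 × (ln 0.4)²) / (1 − 0.5) = 725 / 0.5 = 1450.

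This is within 6 of 1444. The R² term allows for overlap between treatment and covariates; it is not a design effect.

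**3. How much the baseline can adjust (six wards assumed).** 480 / 6 = 80 admissions per ward, and 80 × 0.05 = 4 expected pADEs. The standard error of a ward's baseline log rate is about 1/√4 = 0.5, as large as the largest between-ward SD assumed below. The baseline is therefore a weak measure of a ward's underlying rate.

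**4. Type I error without adjustment, closed form.** Intervention-phase admissions per ward: 964 / 6 ≈ 160.7. With between-ward log-rate SD σ, design effect ≈ 1 + 160.7 × 0.05 × σ², and type I error = 1 − Φ(1.645 / √DE).

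- σ = 0.3: DE 1.72, error 10.5%
- σ = 0.5: DE 3.01, error 17.1%

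**5. Type I error by simulation.** Six wards in three centres, 80 baseline and about 161 intervention-phase admissions per ward, rate 5 per 100, no true effect, nominal one-sided 5%, 2,500 runs per row (simulation standard error about 0.6 points at an error of 10%). The SDs are assumptions.

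| Ward SD | Ward-by-period SD | Site + treatment | Site + ward baseline rate + treatment | Ward indicators + period + treatment |
|---|---|---|---|---|
| 0 | 0 | 4.3% | 4.1% | 5.2% |
| 0.3 | 0 | 11.2% | 9.2% | 5.2% |
| 0.5 | 0 | 19.8% | 11.6% | 5.9% |
| 0.3 | 0.3 | 15.4% | 14.3% | 9.1% |
| 0.5 | 0.3 | 20.6% | 15.6% | 9.4% |

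The fourth column is closest to the article's covariate list. Ward indicators restore the nominal level only if wards do not drift between periods.

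**6. Power of the ward-indicator model (six wards, rate ratio 0.4).** Expected pADEs: 240 × 0.05 = 12 per arm at baseline; 482 × 0.05 = 24.1 and 482 × 0.02 = 9.64 in the intervention phase.

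SE(log rate ratio) = √(1/12 + 1/12 + 1/24.1 + 1/9.64) = √0.312 = 0.56

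Power = Φ(0.916 / 0.558 − 1.645) ≈ 50%; simulation gives 48 to 50%. The article states 80%.

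A ward-by-period SD of 0.3 adds about 4 × 0.09 / 3 = 0.12 to the variance, giving SE √0.432 = 0.66 and power Φ(0.916 / 0.657 − 1.645) ≈ 40%, before any small-sample correction.

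**The case against.** The strongest reply is that the baseline phase exists precisely to handle ward differences. The covariate list is open, so a model with ward indicators and period is compatible with the text, and it holds about 5% error if ward differences are stable. The quoted sentence describes what the sample size permits, and a robust variance could sit in an unseen analysis plan. The size of the inflation also rests on assumed variances.

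Much of this is fair. The text does not exclude ward indicators, and no one can state the true inflation from this article. But the text does not specify them either. If they were intended, the stated 80% power does not go with them (step 6), and nothing in the article deals with wards changing between periods.

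Several stronger readings are tempting and not supported:

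- **A false positive is likely.** The calculations show an error above the nominal 5%, not one that is probable.
- **The ward-level covariates use up all six wards.** The stated model covers both periods, which gives 12 ward-period cells. The number of wards and the levels of ward type are not fixed in the article.
- **A randomisation test can never reach 0.05.** The minimum one-sided p is 1/2³ = 0.125 only with exactly two wards per centre. With three per centre it is 1/27 = 0.037.
- **The cost-effectiveness ratio is invalid.** Too-small standard errors do not alter the point estimate of the pADE difference, only its stated uncertainty.
- **All inflation in any baseline-adjusted fit is clustering.** If the baseline count is both a covariate and part of the outcome rows, the test rejects about 7 to 8% with no ward variation at all. The table avoids this by using the baseline only as a covariate.

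**Conclusion.** The point stands: the unit of randomisation is the ward, while the stated model and both sample sizes use the admission as the independent unit. The match to 962 and 1450 shows that no allowance for clustering was built in.

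For a model close to the one described, the one-sided type I error is about 9 to 16% instead of 5%. This rests on six wards of equal size, a ward log-rate SD of 0.3 to 0.5 and a ward-by-period SD of 0 to 0.3, none of which the article gives. Smaller variation would mean less inflation, and none at all if wards did not differ. More control wards would ease the problem but not remove it, since there are still only three intervention wards.

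The primary p-value and interval, the stated power and the uncertainty of the cost-effectiveness ratio are too optimistic as written. This should be corrected before the arms are compared.

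**What to change.** In Sample size and data analysis:

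1. Specify a Poisson model with ward indicators and period, with treatment defined as intervention ward by intervention period. The ward indicators take the place of site, ward type and baseline ADE level; patient covariates such as age can stay.
2. Specify ward-level inference: either a ward-by-period random effect or a ward-level analysis of the change in rate, with small-sample degrees of freedom.
3. Report the pADE rate for every ward and period, and base the conclusion on the interval from this analysis. Carry the same uncertainty into the cost-effectiveness analysis.
4. Restate the power, and let the planned recalculation state an assumed between-ward and ward-by-period variance as well as the base rate.
5. A randomisation p-value may be added as supportive, with its minimum stated for the actual number of wards.

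The analysis change needs no new data, but it is more than a change of wording. The interval widens, and the stated power falls from 80% to about 48 to 50% with six wards, and lower if wards drift. The small baseline is a large part of this: it contributes 2/12 = 0.167 of the 0.312 variance in step 6. Recovering power would mean a larger baseline or more wards, which is a decision for the sponsor at the recalculation.

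### The sample sizes for the pADE count leave no margin for overdispersion, and the named Poisson analysis should carry a variance that allows for it

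*Protocol article*

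**What the plan says.** Under Study outcomes and data collection, the protocol article defines the primary outcome as an event count: "The primary outcome parameter is the number of preventable ADEs per 100 admissions". The patient-level version, "number of patients with preventable ADEs per total number of admissions", is listed separately as a secondary outcome. One patient can therefore contribute more than one event to the primary outcome.

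Under Sample size and data analysis, the planning values are:
- Control rate: "We expect a mean base rate of five preventable ADEs per 100 admissions in the control group".
- Effect: a fall from 5 to 2 per 100, a rate ratio of 0.4.
- Size: "a sample of 964 admissions achieves 80% power at a 0.05 one-sided significance level", with equal allocation.

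The same section then says that the full 1444 patients (480 baseline plus 964) support "a Poisson regression of the number of pADEs with the type of treatment (intervention or control) as the main covariate of interest", with 80% power at 0.05 even if other covariates explain 50% of the variance. It mentions no dispersion parameter, negative binomial model or robust variance. The section closes by planning to recalculate the sample size once baseline pADE counts are known. The only reason given is uncertainty about the control rate.

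The Discussion lists influences on ADE risk, among them "patient-specific factors (e.g. number of medications taken", and says that the extent of their influence is unknown.

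**The concern.** Poisson regression with its default standard errors takes the variance of the count to be equal to its mean. If patients differ in underlying risk in ways that the model does not capture, the variance exceeds the mean. Two things follow.

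1. Standard errors that rely on the Poisson assumption are then too small, and the one-sided 5% test rejects too often.
2. Even with corrected standard errors, the sample delivers less than the stated 80% power, because the required number rises in proportion to the dispersion.

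The issue concerns variation between patients. It is separate from correlation within wards, and dealing with wards alone would not necessarily resolve it.

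**Working it through.** **Inputs.** From Sample size and data analysis: control rate 0.05, intervention rate 0.02, 964 admissions (482 per arm), one-sided 0.05, 80% power, 1444 in total, covariate R² 0.5. The dispersion φ (variance divided by mean) is not in the document. It is assumed here and shown over a range.

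**Step 1: reproduce 964.** For the difference of two Poisson rates with variance equal to mean,
n per arm = (1.645 + 0.842)² × (0.05 + 0.02) / 0.03² = 480.9, so 481 per arm or 962 in total, against 964. Power at 482 per arm is Φ(0.03/√(0.07/482) − 1.645) = 80.1%.

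**Step 2: reproduce 1444.** Use the Signorini formula for Poisson regression with treated share 0.5, B = ln 0.4 and φ = 1:
N = (1.645 × √4 + 0.842 × √7)² / (0.05 × B²) / (1 − 0.5) = 1450, against 1444. Power at 1444 is 79.9%.

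The article does not name its formulas. Other one-sided formulas without a dispersion term gave 452 to 528 per arm. The two above match closely, and within them the figures come out only with φ = 1. The 50% allowance is for covariates correlated with treatment and is not a dispersion term.

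**Step 3: what φ might be.**
- *Repeats under Poisson itself.* At a mean of 0.05, the share of affected patients with two or more events is 1 − 0.05e^(−0.05)/(1 − e^(−0.05)) = 2.5%. Repeats are thus compatible with φ = 1.
- *Differences in patient risk.* φ = 1 + mean × CV², where CV is the coefficient of variation of risk between patients. At 0.05, CV = 1 gives φ = 1.05; φ = 1.5 needs CV = √(0.5/0.05) = 3.2.
- *One in five affected patients has exactly two events (assumption).* Per affected patient, the mean is 1.2 and the mean square is 0.8 × 1 + 0.2 × 4 = 1.6. Then φ = 1.6/1.2 − 0.05 = 1.28 at the control rate.

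**Step 4: consequences.** One-sided error with unscaled Poisson errors = 1 − Φ(1.645/√φ). Power at 964 with the correct variance = Φ(0.03/√(φ × 0.07/482) − 1.645). Total for 80% power = 2 × φ × 480.9, rounded up per arm. Power of the 1444 regression uses the step 2 formula with φ as a multiplier.

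| φ (assumed) | One-sided error, unscaled | Power at 964 | Total for 80% | Power of 1444 regression (R² 0.5) |
|---|---|---|---|---|
| 1.00 | 5.0% | 80% | 962 | 80% |
| 1.05 | 5.4% | 78% | 1010 | 78% |
| 1.10 | 5.8% | 77% | 1058 | 77% |
| 1.28 | 7.3% | 71% | 1232 | 72% |
| 1.50 | 9.0% | 65% | 1444 | 68% |

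A simulation of the one-in-five scenario (482 per arm, equal rates, unscaled Poisson test) gave a one-sided error of 7.3%.

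The table applies the same φ to both arms. Under a negative binomial model φ is smaller at the lower rate. With φ = 1.5 at 0.05 it is 1.2 at 0.02, and the variance term becomes 0.05 × 1.5 + 0.02 × 1.2 = 0.099 instead of 0.105. Power is then 67% instead of 65%.

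**Step 5: what baseline can tell.** 480 × 0.05 = 24 expected events. Simulating the one-in-five scenario, 95% of dispersion estimates from 480 admissions fall between 1.04 and 1.52, so a single estimate is imprecise.

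**The case against.** The strongest objection is that the article names a model family and not a variance estimator. Its sentence on the regression is about feasibility and power, and its covariate list is only illustrative. An analysis plan that is not shown could specify robust or scaled errors without contradicting anything printed. This stands as far as the error rate is concerned: a reader might infer that the 5% test is not a 5% test, but that holds only if model-based errors are used. It does not rescue the power, since 964 and 1444 are stated as achieving 80% and no choice of standard error restores that if φ exceeds 1.

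A reader might also infer that, because events and affected patients are separate outcomes, the plan expects repeats and the Poisson assumption must fail. The document does not support this. It gives no repeat rate, and Poisson counts include repeats. The better evidence is the statement on patient-specific risk factors, but that gives no size. Risk varying with CV 1 produces only 1.05. Organisational factors act largely at ward level, and adjustment for site, ward type, period, baseline level and age would remove part of the heterogeneity.

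Finally, power may be better than planned for other reasons. If the control rate were 7 per 100 with the same rate ratio, power at 964 would be 83% even at φ = 1.28. If covariates explained 30% instead of 50%, the 1444 regression would have 82% power at φ = 1.28. Both are possible, neither is assured, and neither protects the error rate of an unscaled test.

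**Conclusion.** The point holds in a conditional form. Both sample sizes are consistent with a variance exactly equal to the mean, and no margin for overdispersion is stated. The article itself gives a reason to expect some extra-Poisson variation between patients. Any φ above 1 lowers power below the figure stated on the plan's own inputs, and raises the one-sided error above 5% if unscaled errors are used.

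The size is uncertain. With mild heterogeneity (φ 1.05 to 1.1) the loss is about 2 to 3 points of power, with a one-sided error of 5.4% to 5.8%. The larger figures, 71% power with 7.3% error at φ = 1.28 and 65% with 9.0% at φ = 1.5, rest on assumed dispersion that the document neither gives nor rules out. The improvement is worth making because it is cheap, not because a large distortion has been shown.

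**What to change.** - Analyse the primary outcome with a negative binomial model, or keep the Poisson rate ratio with a robust or dispersion-scaled variance, alongside the ward terms. If an analysis plan already does this, a sentence in the protocol saying so is enough.
- State next to the 964 and 1444 figures that the 80% power assumes no overdispersion.
- In the recalculation already planned after baseline, vary the dispersion as well as the control rate. Use a range of values informed by the baseline counts instead of one point estimate, since about 24 events are expected.

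The endpoint, design and data collection do not change. The analysis change costs a slightly wider interval, and little if φ is close to 1. Holding 80% power under overdispersion costs more than wording: by the difference formula, the parallel comparison would need 1058 admissions at φ = 1.1 and 1232 at φ = 1.28. The alternative is to keep 964 and report the lower power.
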